## Abstract

**Background:**

Pain after surgery is normal, and treatments, including both pharmacological and psychological components, are fundamental for proper postoperative care. While several trials have investigated the analgesic effect of traditional non-pharmacological treatments, such as cognitive behavior therapies, the newer ways of delivering psychological interventions for pain after surgery are scarcely investigated. The aim of this randomized controlled trial (RCT) is to determine if delivering the psychological content through virtual reality (VR) along with the standard pharmacological treatment return better pain relief outcomes than standard care in adult patients following surgery.

**Methods:**

This is a protocol of a parallel RCT conducted in one community hospital. In order to test the efficacy of VR environments for reducing pain intensity, in the following day after surgery, adults (18 to 65 years) will be randomly assigned to either (1) standard treatment after surgery (control group) or (2) VR based intervention along with standard treatment. It is intended that a minimum of 30 patients be recruited in each group. For estimating the intensity of pain, both self-report and physiological measures will be used. Repeated measures of pain outcomes will be taken before and after the intervention. Moreover, for allowing an in-depth investigation of the effect of VR environments, the primary outcome will be complemented with measures of the adverse effects, level of immersion, and level of presence in the VR environment.

**Supplementary Information:**

The online version contains supplementary material available at 10.1186/s13063-021-05196-7.

## Background

As defined by the International Association for the Study of Pain (IASP), pain is an unpleasant sensory and an emotional experience associated with actual or potential tissue damage or described in terms of such damage [1]. Often, acute pain results from trauma or surgery and represents a warning of the brain that noxious stimuli are present or tissue is continually affected [2]. Whereas symptoms of acute pain decrease after cessation of painful stimuli, chronic pain symptoms remain beyond the recovery expected time and often continue despite treatment of initial tissue damage [1]. A report [3] based on data from National Health Interview Survey (NHIS) Sample Adult Core and the NHIS Adult Functioning and Disability Supplement pinpointed that in the year of 2012, 86.6 million US adults reported pain in some days in the last 3 months while 25.5 million reported having chronic (daily) pain. Similarly, a subsequent analysis conducted on 300 post-surgical patients [4] relived that up to 85% of people experienced acute postoperative pain, respectively pain severity was rated as moderate, severe, or extreme in 75% of those cases. Besides, acute postoperative pain was associated with prolonged hospitalization [5], alveolar ventilation, tachycardia, insomnia, and flawed wound healing [6], as well as with an increased risk of chronic post-surgery pain (CPSP) [7]. Described as the pain which persists beyond the expected recovery time after a surgical procedure [8], CPSP is reported in 10% to 70% of cases depending on the type of surgery [7, 9, 10], and several biological and psychological factors [11, 12].

Despite that in the last years pain management gained a lot of attention in both research and practice areas with enormous gains, the management of postoperative pain remains a tremendous challenge with high costs for patients and health care providers [4]. Current clinical guidelines for postoperative pain management recommend evidence-based treatments including pharmacological and psychological components [5]. The large majority of non-pharmacological components for postoperative care are interventions based on cognitive behavioral therapy (CBT) which had proved their efficacy in decreasing pain and distress in different surgical settings, such as lumbar spinal fusion [6, 7], abdominal surgery [8], cardiac surgery [9], or orthopedic surgeries [10]. These results were complemented with the findings of a recent meta-analysis [11] estimating the effectiveness of psychological interventions on postoperative pain management after orthopedic surgery, with medium effect sizes for decreasing pain intensity (Hedges’*g =* 0.31, 95% confidence interval (CI) 0.14 to 0.48) as for improving recovery (Hedges*’g =* 0.38, 95% CI 0.22 to 0.54). However, these CBT interventions were delivered into face to face format and consequently associated with several threats regarding their applicability on a large scale. Specifically, one of the biggest challenges of the face to face interventions is to synchronize the hospitalization time and patients’ availability, as some were designed to be implemented in pre-surgical settings. Likewise, other interventions need several sessions to be implemented before producing positive effects, and often patients did not have this amount of time during their hospitalization. As a consequence, most of the CBT interventions are applied only in the management of chronic pain while the treatment of acute pain remained mainly pharmacological [12]. Further, the consequences of treating pain mainly through pharmacological options are the array of side effects derived from opioids consumptions such as vomiting, nausea, respiratory depression, and physical dependence [7, 8] which are increasing the costs of pain care and place pain medicine in a peerless crisis [9].

One potential approach for increasing the applicability of CBT interventions in cases of acute pain during short hospitalization could be to develop shorter protocols, respectively to deliver the psychological content through technology, such as virtual reality (VR). The VR technology already proved its effectiveness in the case of adults in other hospital settings, such as burn units [13–15] or cancer units [16–19], and is currently under evaluation for pain relief during venipuncture in pediatric patients [20].

By using a combination of technologies (i.e., head-mounted display-HMD, vibro-tactile gloves, individualized sounds, and gesture-sensing joysticks), VR environments create immersive [21] and multi-sensorial experiences [22]. Immersion in the virtual world is believed to facilitates the shifting of attention away from the painful stimuli or from the experience of pain, to more engaging or enjoyable stimuli, developing effective distraction strategies and reshaping the pain perception [23, 24]. A recent meta-analysis [25] estimating the efficacy of VR interventions for acute pain management in clinical settings found a medium effect size of these interventions (standard mean differences (SMD) *=* − 0.49, 95% CI − 0.83 to − 0.14). Moreover, a subsequent meta-analysis [26] relying only on randomized controlled trials (RCT) conducted in hospital settings showed significant effects of VR-based interventions to reduce pain intensity during medical procedures (7 studies, Hedges’*g* = 1.09, 95% CI 0.25 to 1.92) and after the medical procedures (12 studies, Hedges’*g* = 1.08, 95% CI 0.46 to 1.70). Moreover, comparable results were founded when interventions aimed to reduce the cognitive (8 studies, Hedges’*g* = 0.82, 95% CI 0.39 to 1.26) or affective components of pain (14 studies, Hedges’*g* = 0.55, 95% CI 0.34 to 0.77). However, these promising results of VR interventions integrated into acute pain management are hampered by the fact that none of the analyses includes studies on post-surgical patients. In spite that the VR technology could be effectively exported in medical care settings [25] as a potentially cost-effective tool [27], to date, in postoperative care, only a few studies examined its efficacy. In this sense, the pain literature discusses the findings of Mosso-Vazquez and colleagues [28] which showed that 30 min of VR exposure can reduce pain intensity after cardiac surgery regardless if the pain relief was self-reported or assessed through physiological measurements (i.e., breathing rate, arterial pressure, and heart rate). Similarly, a subsequent study of Mosso-Vazquez and colleagues [29] comparing two different VR devices (i.e., HMD and mobile VR) for pain relief during ambulatory surgery revealed that both technologies decreased pain intensity, with better results for VR environments delivered through HMD. This result is consistent with other results proving that high-quality VR environments create a better distractor from pain [30] although the estimates were not in postoperative settings. Nevertheless, while these studies conducted by the Mosso-Vazquez and colleagues [28, 29] had positive and clinically significant results, highlighting the potential usefulness of VR in postoperative pain management, these studies were uncontrolled and possibly accompanied by overestimations of the VR efficacy. As far as we know, to date, there are no studies estimating the effectiveness of VR for postoperative pain following surgery under general anesthesia in a randomized clinical manner. In addition, the VR contents used in previous studies were intended only to distract patients from pain. Using environments that promote relaxation stimuli rather than distraction stimuli can be particularly useful because a relaxed state of mind was associated with a reduced demand of tissue oxygen and a reduced level of lactic acid, both being harbingers of a decreased level of pain [31]. In addition, relaxation was associated with an increased level of endorphins, lower levels of anxiety, and skeletal muscle tension. As such, the present protocol proposes a randomized controlled trial, to assess the effectiveness of relaxing VR environments for pain relief at patients in the first days after surgery.

## Objectives

The aim of this study is to assess whether exposure to relaxing VR environments is associated with decreased levels of pain after surgery after varicose veins, hernia repair, or gallbladder surgeries. Surgeries of varicose veins, hernia repair, and gallbladder were aggregated due to similarities across (1) the incidence rate [32–34], (2) levels of pain intensity after surgery [35–37], and (3) odds of acute pain to be translated into CPSP [35–37]. We hypothesize that VR-based intervention will have a better result in decreasing pain when it is used as a complementary treatment of standard care compared with the standard care alone. Additionally, we will assess the safety of VR-based intervention in patients after surgery.

## Methods and analysis

### Study design

This study is a prospective, randomized controlled trial with two parallel groups. After randomization, participants will receive either (1) standard care after surgery (control group) or (2) VR-based intervention along with standard care treatment (experimental group).

The study protocol follows the Standard Protocol Items: Recommendations for Interventional Trials (SPIRIT) [38] instructions and received the ethical approval from the Babes-Bolyai University committee as from the committee of Municipal Hospital of Cluj-Napoca and was retrospectively registered on ClinicalTrials.gov (NCT03776344).

### Study sample size

Using G*Power 3.1.9.2 [39], we had estimated a minimum of 50 participants (25 in each group) needed to detect an effect size of 0.49, with *α* = 0.05 and power = 0.80. The expected effect size of 0.49 was chosen in the light of the results found by the most recent meta-analyses [25, 26], being a conservative effect size given that in their analysis Chan and colleagues [25] found a medium effect size (SMD = − 0.49, 95% CI − 0.83 to − 0.14) and the analysis of Georgescu and colleagues [26] a large effect size was found (Hedges’*g* = 1.08, 95% CI 0.46 to 1.70) for studies with parallel design aiming to decrease pain at hospitalized patients. However, as we expected some dropouts (based on other studies using VR systems for treating anxiety [40]) and some incomplete or unusable data, especially on the physiological measure, we aim to recruit 30 participants in each group.

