### Randomization and blinding

Randomization was conducted within the type of surgery using a random number generator, with an equal number of participants in the control and experimental group. An independent researcher had conducted the randomization sequence and the allocation sequence was stored on a secured computer until the participants were assigned to one of the interventions. The medical personnel and trial assessors were blind to the group allocation, but the study participants and research assistant were aware of the allocations. Precaution strategies to prevent the blind from breaking up included a limited number of persons interacting with the patients (i.e. only the research assistant) and a reminder to the patients not to talk about research allocations and study procedure. In addition, the treatment room was a different room of the patient hospital room. In the treatment room patients from the experimental group was exposed to the VR content and psychological respectively physiological measured. For the patients from the control group, only psychological and physiological measures were taken without exposing them to the VR content. After this, each participant was conducted to their hospital room. In the case that a participant explicitly requests to end the study procedure for any reasons, the procedure was stopped and counted as a dropout. Those patients who ask to end the procedure earlier were asked to respond at a short interview to quantify the reasons.

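### The stated inputs (standardised difference 0.49, alpha 0.05, power 0.80, two equal groups) do not give 25 per group

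*Protocol article*

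**What the plan says.** Under Study sample size, the protocol article states that "we had estimated a minimum of 50 participants (25 in each group) needed to detect an effect size of 0.49", with alpha set at "0.05 and power = 0.80", using G*Power.

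On the origin of the effect size it says "The expected effect size of 0.49 was chosen in the light of the results found by the most recent meta-analyses". One of the two meta-analyses "found a medium effect size (SMD" = −0.49, 95% CI −0.83 to −0.14). The other gave Hedges' g = 1.08. The article calls 0.49 conservative on that basis.

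The target is then raised to 30 per group to allow for dropouts and unusable data. The Abstract repeats it: "It is intended that a minimum of 30 patients be recruited in each group".

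The design is a "prospective, randomized controlled trial with two parallel groups", randomised "with an equal number of participants in the control and experimental group". Under Main analyses, pain intensity is to be analysed by a random coefficient model with time, group and their interaction.

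**The concern.** A standardised mean difference of 0.49 between two parallel groups is a moderate effect, and 25 per group is small for it. The sample-size paragraph claims no design gain, such as a pre-post correlation, that would reconcile the two. Effect size, alpha, power and sample size are all printed, so the claim can be checked directly.

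The stake is interpretation. If the 80% figure stands, a non-significant result on the primary outcome would look like reasonable evidence against an effect of 0.49, which the article presents as a cautious assumption. The design supports that reading only if pain before and after the session is very highly correlated.

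**Working it through.** **Inputs from the article.** Standardised difference d = 0.49; alpha 0.05; power 0.80; two equal parallel groups; 25 per group as the calculated minimum and 30 per group as the recruitment target. Sidedness is not stated. Two-sided is taken as the default, and one-sided is also shown because the hypothesis is directional: "We hypothesize that VR-based intervention will have a better result in decreasing pain".

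**Step 1: try to reproduce 25 per group.** Normal approximation, n per group = 2(z_alpha + z_power)² / d²:
- Two-sided: 2(1.960 + 0.842)² / 0.2401 = 65.4, so 66. The exact noncentral t gives 67 (power 0.804).
- One-sided: 2(1.645 + 0.842)² / 0.2401 = 51.5, so 52. The exact noncentral t gives 53 (power 0.805).

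The one-sided 53 is per group, 106 in total, so it does not explain a total of 50.

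**Step 2: power at the stated sizes.** Noncentral t with noncentrality d√(n/2) and 2n − 2 degrees of freedom:
- n = 25: 0.49 × √12.5 = 1.73. Power is 0.397 two-sided and 0.525 one-sided.
- n = 30: 0.49 × √15 = 1.90. Power is 0.463 two-sided and 0.591 one-sided.

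The smallest d with two-sided 80% power is 0.81 at 25 per group and 0.74 at 30 per group.

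**Step 3: the planned time-by-group contrast.** With one measurement before and one after, the interaction compares mean changes between groups. If r is the pre-post correlation and the variances are equal, a change has SD √(2(1 − r)) in units of the single-score SD. The effect entering the test is therefore 0.49 / √(2(1 − r)). ANCOVA on baseline replaces that divisor by √(1 − r²) and uses 2n − 3 degrees of freedom. The values of r are assumptions, because the article gives none. Two-sided power:

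| Assumed r | Change contrast, 25 per group | Change contrast, 30 per group | ANCOVA, 25 per group | ANCOVA, 30 per group |
|---|---|---|---|---|
| 0.3 | 0.300 | 0.351 | 0.428 | 0.498 |
| 0.5 | 0.397 | 0.463 | 0.500 | 0.577 |
| 0.7 | 0.592 | 0.673 | 0.661 | 0.743 |
| 0.8 | 0.765 | 0.839 | 0.807 | 0.875 |

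For 80% power at 25 per group, the change contrast needs r = 0.82 and ANCOVA r = 0.80. At 30 per group the values are 0.78 and 0.75.

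**Step 4: where might 50 come from?** Other readings of the inputs miss it. A paired t-test needs 35 pairs two-sided or 28 one-sided. Taking 0.49 as Cohen's f in a one-way ANOVA gives 35 in total, or 36 in equal groups. Taking it as a correlation gives about 30.

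One routine does return 50: G*Power's repeated-measures within-between interaction, with f = 0.49/2 = 0.245 and r of about 0.27 to 0.29. For example, at r = 0.28 the noncentrality is f² × N × 2/(1 − r) = 0.0600 × 50 × 2/0.72 = 8.3. However, in a two-group, two-time interaction f = 0.245 means each cell deviates by 0.245 SD, so the between-group difference in change is 4 × 0.245 = 0.98 SD, twice the stated effect. A difference in change of 0.49 SD corresponds to f = 0.49/4 = 0.1225. With N = 50 that gives power 0.397 at r = 0.5, 0.592 at 0.7 and 0.765 at 0.8, matching the change-contrast column for 25 per group.

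**The case against.** The strongest reply is that the trial does not plan a two-sample t-test on post-session scores. The primary model uses pain before and after a 15-minute session, and two ratings so close together could be highly correlated. At r = 0.8 the change contrast has 77% power with 25 per group and 84% with 30. This stands as a limit on what can be said: the trial's real power is not known from the article. It does not rescue the 80% claim, because the article states no correlation and 25 per group still falls short at 0.8 on the planned contrast.

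A reader might therefore infer too much: that the trial has 40 to 46% power and is more likely than not to miss the assumed effect. The document does not support that as a flat statement. Sidedness is open, and one-sided power is 53% and 59%. ANCOVA at r = 0.5 with 30 per group gives 58%, and either baseline-using analysis at r = 0.7 is above one half. The 40 to 46% figures belong to a two-sided comparison without a gain from baseline, or to the change contrast at r = 0.5.

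A second reply is that 50 can be obtained from G*Power's repeated-measures routine. That is true and is a possible origin, though the article does not say so. It would mean a conversion error rather than a slip of arithmetic, with the sample sized for twice the effect reported.

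A third reply is that a condensed article may leave test, sidedness and correlation to a fuller document. Granted: their absence is not the point here. The point is that the printed effect size, alpha, power and sample size do not fit together.

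Finally, recruitment ended in September 2019, so the sample size cannot change. That limits the remedy to the statement and its use in interpretation.

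**Conclusion.** The sample-size statement is wrong on its own inputs. For a between-group standardised difference of 0.49 at alpha 0.05, 80% power in a two-sample comparison takes 67 per group two-sided or 53 one-sided, more than twice the 25 stated. With 25 (30) per group that comparison has 40% (46%) power two-sided or 53% (59%) one-sided.

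For the planned time-by-group contrast, two-sided power with 25 to 30 per group runs from about 30–35% at r = 0.3 to 77–84% at r = 0.8. The claimed 80% at 25 per group holds only if r is about 0.82, or about 0.80 under ANCOVA.

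These figures assume equal groups, equal variances before and after, 0.49 expressed in SDs of a single pain score, and 25 or 30 evaluable patients per group. Because 30 includes the allowance for loss, the 30-per-group figures are the favourable end.

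**What to change.** Rewrite the power statement under Study sample size; no extra patients are requested.

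- Replace the 80% claim with the power that 25 to 30 evaluable patients per group gives for d = 0.49. Name the test, the sidedness and the assumed pre-post correlation, and show the range: for the two-sided time-by-group contrast, about 30% (35%) at r = 0.3, 40% (46%) at 0.5, 59% (67%) at 0.7 and 77% (84%) at 0.8, for 25 (30) per group.
- State that, without a gain from baseline, two-sided 80% power holds only for d of about 0.81 (25 per group) or 0.74 (30 per group).
- State that a non-significant result is inconclusive for effects near 0.49 and will be reported with its 95% confidence interval.
- If the repeated-measures routine was the source of 50, say so and correct the effect-size conversion.

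The cost is a change of wording and a less favourable power figure. The Trial status section reports that data analysis had not been performed, so on that account the correction could be made before results are known.

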### Participants

All the participants were recruited from one community hospital from Romania. Starting October 2018, each patient admitted to the hospital for surgery was screened for eligibility criteria to this trial.

### Inclusion/exclusion criteria

The below criteria had to be cumulative met in order that a participant be included in the trial.

#### Inclusion criteria

❖ Adults aged 18–65 years, after surgery of varicose veins, hernia repair, or gallbladder surgery.❖ Patient in the acute care units, 1–3 days following surgery.❖ Willing and able to provide informed consent and participate in the study visit and study follow-up questionnaire.

Presence of any criteria listed below will conduct at the exclusion of the participant from the trial.

#### Exclusion criteria

❖ Patients with neoplastic pathologies.❖ Patients with a history of motion sickness.❖ Patients with severe visual impairment (i.e., not able to clearly see without glasses; patients with contact lenses will not be excluded).❖ Patients with severe/profound cognitive impairments measured with Six-item Cognitive Impairment Test (6CIT).❖ Use of strong opioids (i.e., morphine)❖ Other reasons for exclusion (Non-Romanian speaking patients, patients with severe psychological problems, etc.)

Some of the exclusion criteria were dependent on the VR device or were designed as a precautionary measure for not harming participants after using VR technology. Particularly, we excluded the participants with profound visual impairments (i.e., those which cannot clearly saw without glasses or without contact lenses) due to the incompatibility with the VR device which was not equipped with the eyes glasses spencer. Similarly, patients with a history of motion sickness were excluded for preventing any severe dizziness or injury.

